## Abstract

**Background:**

Motivational interviewing (MI) could be a method for minimizing alcohol-related harm. The study aims to assess the effectiveness of a brief intervention, based on a MI, in patients with risky alcohol use attended in Primary Care (PC).

**Materials and methods:**

A cluster-randomized, two-arm parallel, multicenter, open-label, controlled clinical trial. Fifty PC healthcare professionals from the province of Córdoba (Spain) will be randomized to one of the two study groups: (1) Experimental Group (EG): MI-based approach; (2) Control Group (CG): Usual care based on health advice. EG intervention: Professionals will receive a training program focused on MI, consisting of a training workshop and the use of pre- and post-workshop questionnaires to measure knowledge and skills acquired, as well as the degree of empathy, with a videotape of the health professionals with standardized patients, before and after the workshop, and subsequent training feedback. CG intervention: Workshop on the management of risky alcohol use based on health advice; participants will also complete the pre-and post-workshop questionnaires and be videotaped. Study population: Patients ≥ 14 years old with risky alcohol consumption (28 Standard Drink Units-SDU-/week in men and 17 SDU/week in women) or excessive alcohol use (≥ 6 SDU in men or ≥ 4 SDU in women, in less than 2 h). It would be necessary to include 110 subjects/group to find a difference of 20% between the percentage of patients in abstinence between EG (37%) and CG (20%), alpha error of 5%, and statistical power of 80%. Assuming a loss rate of 5% and the cluster design effect, the number of subjects to be recruited is estimated at 197/group. The follow-up period will be 12 months. The primary outcome variables will be the self-reported alcohol use level and the Alcohol Use Disorders Identification Test (AUDIT) questionnaire score.

**Discussion:**

The study aims to demonstrate the effectiveness of the motivational approach in the comprehensive treatment of the patient with risky alcohol use, improving the empathy of the healthcare professionals and strengthening the healthcare professional-patient relationship to achieve the behavioral change of the patients with this problem in primary care consultations.

**Clinical trial registration:**

ClinicalTrials.gov.

## 1. Introduction

Alcohol consumption is one of the main causes of morbidity and mortality (1, 2). According to the World Health Organization (WHO), alcohol consumption caused approximately 3 million deaths worldwide in 2018 (5.3% of all deaths) and 132.6 million disability-adjusted life years (DALYs) (3). In the latest Global Status Report on alcohol and health published by the WHO, it is also mentioned that mortality resulting from alcohol consumption is higher than that caused by diseases such as tuberculosis, HIV/AIDS and diabetes. 1.2 million deaths from digestive and cardiovascular diseases (0.6 million for each condition) and 0.4 million deaths from cancers are related to harmful use of alcohol. Furthermore, risky alcohol use leads to disorders that cause family problems (such as mistreatment, unplanned pregnancy, separation) and economic and social consequences (unemployment, accidents, violence, homicides), and complicates the evaluation and treatment of other medical and psychiatric conditions (4).

In Spain, it is estimated that 4 million people have risky alcohol use and 2 million people meet criteria for alcohol dependence (5). According to the last Survey on Alcohol and Drugs in Spain (EDADES) (6), alcohol was responsible for 3.6% of deaths in 2017. Due to the individual and collective impact it causes, harmful alcohol consumption accounts for 15–20% of the consultations attended in Primary Care (PC). For this reason, PC healthcare professionals play a crucial role in the detection and care of patients with alcohol-related disorders by taking a comprehensive and personalized approach to lifestyle habits and toxic substance use (7).

In the GBD 2016 Alcohol Collaborators study published in August 2018 (8), in which a systematic analysis of alcohol use was performed in 195 countries from 1990 to 2016, it is concluded that alcohol consumption is an important risk factor for the global burden of disease and causes a substantial loss of health. It also determines that the risk of all-cause mortality, and specifically cancer, increases with higher levels of consumption, and that the level of consumption that minimizes loss of health is zero. In this study, an estimated 2.8 million deaths were attributed to alcohol consumption in 2016. Globally, alcohol consumption was classified as the seventh risk factor for premature death and disability in 2016. Among the population aged 15 to 49 years, alcohol consumption was the main risk factor for the overall burden of disease, causing 8.9% of DALYs (a useful measure for quantifying healthy life losses, either by premature mortality or by the time lived with reduced health) for men and 2.3% for women. In this same population, 3.8% of female deaths and 12.2% of male deaths were attributable to alcohol consumption. For populations aged 50 years and older, 27.1% of the total number of female deaths and 18.9% of male deaths were attributable to alcohol. In addition, the results of this study indicate that alcohol consumption and its harmful health effects could become a growing challenge. Therefore, it is crucial that alcohol control policies are enacted or maintained today to prevent the potential increase in alcohol consumption in the future (9).

Effective policies could now generate significant health benefits for the population in the coming years (10).

Despite the prevalence of this health problem, the intervention rates of PC health professionals in alcohol management are consistently low (11). In addition, a Cochrane review on the effectiveness of brief intervention in PC concludes that such brief interventions lead to a 12.3% reduction in the average alcohol consumption among those receiving it (12).

Similarly, it is also reflected in the literature that the implementation of motivational interviewing (MI) in PC is an effective communicational tool for addressing health problems (13–15), such as hypertension (16), dyslipidemia (17), or addictions, such as alcohol consumption (10). Although MI began to be applied in the management of risky alcohol use (10), there is little evidence about the actual effectiveness of MI in reducing alcohol-related harm in Spanish primary care centers. Given that the population assisted in primary care differs from the population assisted in the hospital setting, it is necessary to assess the effectiveness of a brief motivational intervention in the management of risky alcohol use in Spanish primary care centers.

The findings from the present study might explain the real benefits of the brief motivational intervention applied on patients with risky alcohol use, as well as making more informed health policy decisions when assigning potentially scarce resources.

## 2. Methods and analysis

### 2.1. Study design

This is a cluster-randomized, two-arm parallel, multicenter, open-label, controlled clinical trial that will be conducted in PC centers of the Andalusian Health Service located in the province of Córdoba (Spain). PC professionals will be randomized to one of two study groups (Figure 1): (1) Experimental Group (EG): Professionals will implement an approach based on brief motivational intervention (18) applied on patients with risky alcohol use, receiving previously a specific training program in this field; (2) Control Group (CG): Professionals will also receive prior training on the management of the patient with risky alcohol consumption and will implement the usual clinical care (health advice) in recruited patients. Participants in both groups will attend a workshop focused on the identification and management of patients with risky alcohol consumption.

**FIGURE 1 F1:**
[figure not shown]
Cluster-randomized trial intervention scheme.

#### 2.1.1. Eligibility criteria

##### 2.1.1.1. Professional selection criteria

Inclusion criteria will be: (1) To be a PC healthcare professional (family physician, nurse or resident internal specialist in Family and Community Medicine or Nursing); (2) To provide informed consent to participate in the clinical trial.

Exclusion criteria will be: Prior MI skills or refusal to participate in the study.

At least 50 healthcare professionals will participate in the controlled clinical trial, each of them will recruit 7–8 patients in PC through opportunistic search.

##### 2.1.1.2. Patient selection criteria

Inclusion criteria will be:

1)To have risky alcohol use (19): (a) Consumption of more than 17 SDU–Standard Drink Units–of alcohol/week (170 grams of alcohol per week), for women; (b) Consumption of more than 28 SDU–Standard Drink Units–of alcohol/week (280 grams of alcohol per week), for men; (c) Patients with a score of 8 points or more in an AUDIT questionnaire; (d) Patients with “binge drinking” (excessive or intensive consumption). That is, males consuming 6 SDU or more or females consuming 4 SDU or more in less than 2 h.2)To be at least 14 years old.3)To provide informed consent to participate in the clinical trial.

Exclusion criteria will be:

1)Severe cognitive impairment (such as severe dementia or psychosis) and/or terminal illness.2)Lack of social support or unemployment.3)Coexistence of another drug dependency supervised by professionals specialized in addictions.

#### 2.1.2. Recruitment

The study will be disseminated through the Multi-professional Teaching Unit of Family and Community Care in the Health District of Córdoba and Guadalquivir. It is intended to recruit at least 15 PC physicians, a minimum of 15 PC nurses, and at least 20 resident physicians and internal nurses from the last year of training. All study information will be sent to the e-mail addresses of existing lists, teaching sessions or face-to-face meetings. Once the objective of the study has been explained, professionals will be invited to participate in the clinical trial and will complete the informed consent forms.

#### 2.1.3. Random assignment

The randomization unit will be the healthcare professional, and the intervention unit will be the patient. Professionals will be randomly assigned and equally (1:1) to one of the two study groups (EG or CG), stratifying according to the center and type of professional. Patients will be recruited through consecutive sampling (opportunistic search of subjects who are treated at participating health centers).

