#### 2.1.4. Intervention planning

Before the intervention, participants will undergo the following training scheme:

-EG and CG will receive a 1-h workshop on the identification, and management of the patient with risky alcohol consumption, based on the recommendations and the algorithm of action proposed by the Program of Preventive Activities and Health Promotion-PAPPS-(20).

-EG: They will receive a 5-h training program to acquire specific MI skills for the management of patients with risky alcohol consumption, which will consist of a workshop, with two video recordings of consultations with simulated standardized patients, one prior to the training and the other after it. Finally, each participant will receive personalized feedback of the video recording from an expert. This program was accredited by the Andalusian Health Quality Agency (ACSA).

-CG: They will not receive the MI training program, instructing them only to perform the health advice they usually do with these patients (based on an informative-persuasive model). They will also be videotaped before and after the workshop to assess its formative impact and that the approach they perform does not present typical characteristics of MI.

The simulated standardized interviews will be conducted by two subjects (one male and one female, both middle aged), with previous experience in performing as actors. Using a role-playing technique, the actors will follow two scripts prepared by two team researchers, experts in the field, and will receive the timely formative feedback before the standardized interviews.

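### Professionals recruit their own patients after allocation and arm-specific training, so the enrolled patients can differ between arms in readiness to change despite randomisation

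*Protocol article*

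**What the plan says.** All of this is in the protocol article.

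- **Unit and blinding.** Section 2.1: "This is a cluster-randomized, two-arm parallel, multicenter, open-label, controlled clinical trial". Section 2.1.3: "The randomization unit will be the healthcare professional, and the intervention unit will be the patient". Allocation is 1:1, stratified by center and type of professional, with no patient-level factor.
- **Training.** Section 2.1 describes the experimental arm (EG) as "receiving previously a specific training program in this field". Of the control arm (CG) it says "Professionals will also receive prior training on the management of the patient with risky alcohol consumption". Section 2.1.4 gives the content: "EG and CG will receive a 1-h workshop on the identification, and management of the patient with risky alcohol consumption". EG then has a further 5 hours on motivational interviewing (MI). CG has none and is told to keep to its usual advice.
- **Recruitment.** Section 2.1.1.1, of the professionals: "each of them will recruit 7–8 patients in PC through opportunistic search". Section 2.1.3: "Patients will be recruited through consecutive sampling (opportunistic search of subjects who are treated at participating health centers".
- **Baseline visit.** Section 2.5.3 has EG professionals rate themselves on the EVEM scale after every visit, and Table 1 marks EVEM at baseline.
- **Safeguards.** Section 2.3 plans a baseline comparability analysis, bivariate tests (chi-square, t test or ANOVA), then regression to control confounders. Table 1 collects stage of change, SDU/day and AUDIT at baseline.
- **Limitations.** Section 3.1.2 names the Hawthorne effect, selection bias from dropout or loss, insincere answers, and confounding to be handled by multivariate analysis.

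**The concern.** When the cluster is a professional and that professional later enrols the patients, randomisation protects the comparison of professionals only. The patients are a post-randomisation selection. If the recruiter knows the arm and has been trained for it, whom the recruiter approaches, and who agrees, can depend on the arm.

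The plausible route here is engagement. MI is a skill in talking with people about change, so MI-trained professionals may bring in more hesitant patients than controls do, or may favour patients who look ready to change. The first would tend to hide a benefit and the second to create one. A larger sample removes neither.

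What is at stake is whether a between-arm difference in drinking can be credited to the intervention rather than to who was enrolled.

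**Working it through.** **Step 1. Order of events.** No dated timeline is given, so the order is inferred.

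| Element | Where | What it implies |
|---|---|---|
| EG trained beforehand, CG given prior training | 2.1 | Training precedes care of study patients |
| 5 h of MI in EG; usual advice only in CG | 2.1.4 | Training reveals the arm |
| EVEM self-rating after every EG visit, marked at baseline | 2.5.3, Table 1 | MI is already in use when a patient enters |
| The professional recruits 7–8 patients | 2.1.1.1 | The recruiter is the randomised person |

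Together these give: randomise, train, recruit. Nothing in the article contradicts that order, and no recruiter blind to arm is described.

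**Step 2. The plan's own sample size.** Section 2.4 uses 37% vs 20%, two-sided 5%, power 80%. With the pooled proportion (0.37 + 0.20)/2 = 0.285:

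n = [1.960·√(2·0.285·0.715) + 0.842·√(0.37·0.63 + 0.20·0.80)]² / 0.17² = 109.5, so 110 per group.

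Design effect = 1 + (15 − 1)·0.05 = 1.7. Total = 220·1.7/0.95 = 393.7, so 394, or 197 per group. The stated figures reproduce and are not in dispute here.

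**Step 3. Illustration of size.** The article gives no figure for selection, so the shift is an assumption. Assume no true effect, CG abstinence 20% (section 2.4), and EG abstinence moved by selection alone. Assume also that the analysis allows correctly for clustering and makes no baseline adjustment.

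Effective n per arm = 197·0.95 / design effect = 187.15 / design effect:
- protocol's design effect 1.7: 110.1
- 7.5 patients per professional, 1 + (7.5 − 1)·0.05 = 1.325: 141.2

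SE = √[(p_E(1 − p_E) + 0.16)/n]; shift = (p_E − 0.20)/SE; P(p < 0.05) = Φ(shift − 1.96) + Φ(−shift − 1.96).

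| EG vs CG | n per arm | SE | Shift | P(significant) |
|---|---|---|---|---|
| 25% vs 20% | 110.1 | 0.0562 | 0.89 | 0.14 |
| 25% vs 20% | 141.2 | 0.0496 | 1.01 | 0.17 |
| 30% vs 20% | 110.1 | 0.0580 | 1.73 | 0.41 |
| 30% vs 20% | 141.2 | 0.0512 | 1.95 | 0.50 |
| 15% vs 20% | 110.1 | 0.0511 | −0.98 | 0.16 |
| 15% vs 20% | 141.2 | 0.0451 | −1.11 | 0.20 |

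The nominal rate is 0.05. Five points is 5/17 = 29% of the planned 17-point difference. The last two rows show that selection the other way distorts the result about as much.

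**Step 4. How such a shift could arise.** Suppose patients ready to change reach abstinence in 40% and others in 10% (assumed). CG at 20% then has (0.20 − 0.10)/(0.40 − 0.10) = one third ready. Each extra 10 percentage points of ready patients in EG adds 0.10·0.30 = 3 points of abstinence. A 5-point shift needs about 17 percentage points more ready patients, which is a sizeable imbalance.

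**The case against.** - **Consent.** A reader might infer that the randomised professionals also take patient consent. Section 2.1.1.2 requires consent but does not say who obtains it. The point rests on recruitment alone.
- **Sampling wording.** A reader might see a contradiction between consecutive and opportunistic. The two can be reconciled: case-finding among attendees, taken in the order they appear. What stands is that no rule obliging every eligible attendee to be invited is stated.
- **Identification.** It is tempting to set 6 hours of training against 1 as a gap in ability to find patients. The identification workshop is the same hour in both arms, the extra 5 hours concern management, and eligibility rests largely on numerical thresholds. The remaining route is engagement and willingness to take part, which is narrower.
- **Readiness is measured.** Stage of change, SDU and AUDIT are collected at baseline, and a comparability analysis and regression are planned. This is a real mitigation. It does not reach motivation beyond what those variables capture, and the bivariate comparison listed first uses none of them.
- **Illustration.** The shifts are assumed, and abstinence is not among the primary patient outcomes in section 2.5.1 (SDU on a typical day, frequency of more than 6 SDU/day, AUDIT score). The figures show sensitivity and do not estimate bias in those outcomes.
- **Ranking.** A reader might call this the main threat to validity. Nothing in the article supports that ranking; self-reported outcomes in an open-label trial are an obvious rival.

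**Conclusion.** The concern holds as a risk of bias, not as a demonstrated imbalance. Open-label professionals are randomised, openly trained for their arm, and then recruit the patients whose drinking is compared. The enrolled patients can therefore differ by arm in readiness to change, and section 3.1.2 does not list this. Its statement that multivariate analysis will control confounding is too strong for this source, because regression covers only what is measured.

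Size and direction are unknown. On an assumed 5-point shift in abstinence favouring EG with no true effect, the chance of a significant result is about 14% with the protocol's design effect of 1.7, or about 17% with 7–8 patients per professional, against 5%. Adjustment for measured readiness would reduce this by an amount the documents do not allow one to state. The conclusion also rests on the inferred order randomise, train, recruit. If patients were in fact enrolled before professionals learned their arm, most of the concern would fall away, and the article should say so.

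**What to change.** 1. **Section 2.1.3.** State that each professional invites every eligible attendee in order until the quota is filled. Keep a log of screened, eligible, declined and enrolled patients, and report it by arm. Cost: a simple form per professional.
2. **Section 2.3.** Make the main between-arm comparison one adjusted for baseline stage of change, SDU and AUDIT, in place of the unadjusted chi-square or t test. All three are already in Table 1. Cost: analysis text only.
3. **Section 3.1.2.** Add recruitment after allocation by unblinded professionals as a limitation, and say that adjustment covers only measured differences. Cost: one or two sentences.
4. **Where feasible,** enrol and baseline-assess patients before allocation is revealed. This gives the strongest protection but is a real trade-off. It separates baseline from the first intervention contact, the 1-, 3-, 6- and 12-month visits must be re-anchored, and the baseline EVEM entry in Table 1 must be reconsidered.

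Items 1 to 3 are worth making even if item 4 is not possible.

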#### 2.1.4. Intervention planning

Before the intervention, participants will undergo the following training scheme:

-EG and CG will receive a 1-h workshop on the identification, and management of the patient with risky alcohol consumption, based on the recommendations and the algorithm of action proposed by the Program of Preventive Activities and Health Promotion-PAPPS-(20).

-EG: They will receive a 5-h training program to acquire specific MI skills for the management of patients with risky alcohol consumption, which will consist of a workshop, with two video recordings of consultations with simulated standardized patients, one prior to the training and the other after it. Finally, each participant will receive personalized feedback of the video recording from an expert. This program was accredited by the Andalusian Health Quality Agency (ACSA).

-CG: They will not receive the MI training program, instructing them only to perform the health advice they usually do with these patients (based on an informative-persuasive model). They will also be videotaped before and after the workshop to assess its formative impact and that the approach they perform does not present typical characteristics of MI.

The simulated standardized interviews will be conducted by two subjects (one male and one female, both middle aged), with previous experience in performing as actors. Using a role-playing technique, the actors will follow two scripts prepared by two team researchers, experts in the field, and will receive the timely formative feedback before the standardized interviews.

### 2.2. Materials and methods

Participants’ information will be obtained from validated tools for assessing risky alcohol use (AUDIT) (21) and the motivational interview (EVEM questionnaire) (22). In addition, the Jefferson (23) scale will be used to assess the empathy of healthcare providers in the management of alcohol use.

-AUDIT (21). Tool designed to identify risky alcohol use that comprises 10 questions divided into 3 conceptual domains. The first domain evaluates recent alcohol consumption and contains three questions (frequency of alcohol use, usual amount of alcohol consumption, and frequency of binge drinking). The second domain assesses symptoms of dependence through three items (loss of control over consumption, increased relevance of consumption and morning drinking). The third domain assesses harmful alcohol use through four questions (feeling of guilt after drinking, memory gaps, alcoholrelated injuries and concerns about drinking). A result equal to or above eight is considered indicative of hazardous and harmful consumption, and a possible alcohol dependence.

-Scale for the assessment of the MI (EVEM) (22). A scale of 14 items with a score of 0 to 4, created to assess encounters between professionals and patients using MI. This scale analyzes: (1) empathy; (2) facilitating patient positioning; (3) working in concordance with the patient; (4) using open questions; (5) performing reflective listening; (6) performing summaries; (7) validating the patient; (8) agreeing on change objectives; (9) promoting action/plan design with the patient; (10) Prevents discord with patient; Global Interview Spirit: (11) evokes; (12) collaborates; (13) honors patient autonomy; (14) shows compassion. This scale has been validated by members of this group (24).

-Empathy Scale (Jefferson Scale) (23), which evaluates three dimensions of empathy: Taking perspective, caring with compassion, and standing in the patient’s shoes. It consists of 20 Likert-type questions with a 7-point response range from strongly disagree (score = 1) to strongly agree (score = 7).

-Knowledge and Attitude Questionnaire: Based on the questionnaire created by our team for a previous study (25), and which was subjected to a process of apparent or consensus logical validity and content validity.

